### Inflammatory markers

3.7

To acquire inflammatory cytokine information, we will implement a dried blood spot (DBS) protocol at both T1 and T2 using microfluid devices that will permit storage of up to 70 μL at each timepoint (280 μL by the end of T2V2). Prior to arriving at the scanner, participants will be instructed to drink as much water as they can to ensure they are properly hydrated; we will also be providing heat pads and blankets to facilitate blood flow. Although unpublished data from our consultant on the grant, [name], has not indicated significant effects of circadian variation on TNF-α in adults with depression, we will use time since wakening and time of sample collection (as well as BMI) as covariates in sensitivity analyses. Samples will be placed in Ziplock bags with a desiccant for storage in a −80 °C freezer. All DBS samples will be assayed for IL-6, TNF-α, and CRP. All extraction and analyses of blood samples will take place at the Institute for Interdisciplinary Salivary Bioscience at the University of California, Irvine (https://iisbr.uci.edu/) in collaboration with co-investigator, [name]. All assays will be tested, in duplicate, using commercially available enzyme-linked immunoassay kits (e.g., IBL International, Hamburg, Germany) following the manufacturers’ protocol without modification. Optical density will be determined at 450 nm using a microplate reader and inflammatory protein concentrations quantified against a five-parameter logistic curve fit generated standard curve. Detection ranges for IL-6, TNF-α, and CRP are 0.08–5.0 pg/mL, 0.31–20.0 pg/mL, and 0.4–10.0 μg/mL, respectively. Intra-assay coefficients of variability range across populations and collection methods, but for past studies using samples collected via DBS, intra-assay coefficients of variability are expected to be <10%. Samples tested outside the detection range for the assay will be retested at a higher dilution to confirm the result.

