### Trier Social Stress Task (TSST)

3.6

A modified version of the Trier Social Stress Task (TSST) will be administered at T1V2 and T2V2. This adapted TSST involves no deception and follows procedures similar to those used by our group in adolescent populations (Ho et al., 2020; Kircanski et al., 2019; Miller et al., 2019). Following the first set of brain imaging acquisitions and the first blood sample collection, participants will be instructed by an experimenter that they will be completing a stress test. There will be two versions of the stress test: a five-minute arithmetic task or a five-minute speech task (regardless of the task, participants will be given 5 minutes of prep time beforehand). Participants will be randomly assigned one of the two stress tests at T1 and will be administered the second stress test at T2 to minimize habituation with repeated testing and ensuring that the order of the two tests are counterbalanced across the sample.

Upon arrival to the session, before, and after the TSST, participants will provide ratings of ten mood states (*Excited, Afraid, Confused, Sad, Energetic, Angry, Happy, Tired, Tense)* based on the Positive and Negative Affect Schedule (PANAS; Crook et al., 1998) on a visual analogue scale from 0 to 10. These ratings will be used as tertiary outcome measures of behavioral responses to social stress. During administration of the TSST, we will also collect saliva samples repeatedly to explore changes in stress hormones before and after an acute stressor. Five saliva samples, each collected approximately 10 minutes apart, will be collected using the SalivaBio Oral Swab Method (Salimetrics, LLC) during the TSST protocol, from which we plan to assay cortisol production. After completing the TSST, participants will complete the remaining scans and provide a secondary blood sample approximately 120 minutes after the first blood sample and then provide a final saliva sample. Additionally, it is possible that secondary stress and anxiety may affect cytokine and CRP levels at Time 1, as this will be the first time most of the participants will have undergone an MRI scan; however, our primary measures of inflammation and glutamate are *within-person differences* before and after the TSST. We will also consider using the PANAS ratings of mood states as covariates in sensitivity analyses.

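### The retest rule sends every out-of-range IL-6, TNF-α and CRP sample to a higher dilution, which cannot resolve or confirm a result below the lower limit

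*Protocol article*

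**What the plan says.** The rule is in section 3.7 (Inflammatory markers) of the protocol article. Three markers are measured in every dried blood spot sample: "All DBS samples will be assayed for IL-6, TNF-α, and CRP". Each has a lower and an upper limit: "Detection ranges for IL-6, TNF-α, and CRP are 0.08–5.0 pg/mL, 0.31–20.0 pg/mL, and 0.4–10.0 μg/mL, respectively".

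The rule for results that miss these ranges is a single sentence: "Samples tested outside the detection range for the assay will be retested at a higher dilution to confirm the result". It does not separate high from low results, and nothing else in the article gives a rule for low ones.

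Two other statements bear on the point. Blood is scarce, since the collection device "will permit storage of up to 70 μL at each timepoint (280 μL by the end of T2V2". Section 3.6 (Trier Social Stress Task) says how the values are used: "our primary measures of inflammation and glutamate are *within-person differences* before and after the TSST".

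**The concern.** Further dilution is a remedy for a sample that is too concentrated for the standard curve. For a sample that is too weak it works in the wrong direction. The rule covers both kinds, and the ranges just before it have explicit lower limits, so a laboratory that followed it literally would dilute samples that are already too weak to read.

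Two things are at stake. First, the purpose of the retest is to confirm the result, and for a low sample it confirms nothing: it comes back below range whether the first reading was right or slightly too low. Second, each such retest spends blood that could have gone to a repeat able to settle the question. Both matter because the primary inflammation measure is a within-person difference, which needs a usable value before and after the stress task. Aims 1 and 2 (section 2) both rest on those changes.

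**Working it through.** **Inputs from section 3.7.** Lower limit L and upper limit U: IL-6 0.08 and 5.0 pg/mL; TNF-α 0.31 and 20.0 pg/mL; CRP 0.4 and 10.0 μg/mL.

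**Assumed input.** The dilution factor of the retest relative to the first test, d, is not stated. I used 2, 4 and 10. Only the relative factor matters, so the dilution used in the first test does not affect the argument.

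**Formulas.** For a sample of concentration C, the concentration presented to the assay after further dilution is C/d. The lowest sample concentration that can still be read is L × d.

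**Samples below the lower limit.** If C < L and d > 1, then C/d < L/d < L, so the sample cannot enter the range whatever d is. Taking C = 0.75 × L and d = 2:

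| Marker | C | C/d | Limit L | In range? |
|---|---|---|---|---|
| IL-6 (pg/mL) | 0.06 | 0.03 | 0.08 | no |
| TNF-α (pg/mL) | 0.2325 | 0.116 | 0.31 | no |
| CRP (μg/mL) | 0.30 | 0.15 | 0.4 | no |

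A sample only just short of the limit fares no better: IL-6 at 0.99 × 0.08 = 0.0792 becomes 0.0396 pg/mL.

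**Effective floor after dilution, L × d.**

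| Marker | Stated limit | d = 2 | d = 4 | d = 10 |
|---|---|---|---|---|
| IL-6 (pg/mL) | 0.08 | 0.16 | 0.32 | 0.8 |
| TNF-α (pg/mL) | 0.31 | 0.62 | 1.24 | 3.1 |
| CRP (μg/mL) | 0.4 | 0.8 | 1.6 | 4.0 |

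**False confirmation.** Suppose the true value lies between L and L × d, and the first reading fell below L through assay error. The diluted sample is then expected to read below L again. For example, IL-6 at 1.05 × 0.08 = 0.084 pg/mL is truly in range, but at 2x it presents 0.084/2 = 0.042 pg/mL. The retest agrees with the wrong first reading. A repeat at the same dilution could have corrected it.

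**Samples above the upper limit.** Here the rule does its job. At 1.5 × U and d = 2, IL-6 goes from 7.5 to 3.75 pg/mL, TNF-α from 30 to 15 pg/mL and CRP from 15 to 7.5 μg/mL, all in range. They are also in range at 4x and 10x.

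**Blood available.** The stated total is 280 μL = 70 μL × 2 collections × 2 timepoints, so 70 μL is the ceiling for each collection. It must serve 3 markers in duplicate, or 3 × 2 = 6 determinations, before any retest.

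**The case against.** The authors probably meant samples above the range, in which case one word is too broad. That is likely, but the text does not say so, and the stated lower limits make the two-sided reading the natural one.

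The weightier objection is about consequence. A sample below the lower limit is already unquantified when first tested. The retest does not create that non-detect, and limiting the rule to high samples would not by itself recover any low value. This stands, and it decides how serious the point is.

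A reader might infer more: that the rule removes pre/post pairs and so shrinks the estimated stress response, perhaps more on the pre-stress side if stress raises the markers. The documents do not support this. Any such loss comes from having non-detects at all and would arise with no retest rule. The article does not say how many samples will fall below range, nor that affected pairs will be dropped or filled with a constant. Its general statement in section 2 is that longitudinal analyses will keep anyone with at least one assessment; that does not settle non-detects, but it gives no support for routine dropping. Their statistical handling may be in an analysis plan that is not shown, so its absence here is no fault and no particular model should be demanded.

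One objection limits the remedy. Section 3.7 says the kits are run to the manufacturer's protocol unmodified, so a lower dilution may not always be permitted. A repeat at the original dilution does not meet that difficulty.

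**Conclusion.** The sentence is wrong as written, and the point is minor. For all three markers, CRP as well as the two cytokines, a retest at higher dilution can neither quantify nor confirm a result below the lower limit. This holds for any dilution factor above 1 and rests only on the stated limits. The size of the shift in the floor depends on the factor, which is assumed: at 2x the floors double to 0.16 pg/mL, 0.62 pg/mL and 0.8 μg/mL.

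The practical harm is an uninformative retest, the use of limited blood, and false reassurance about non-detects in a primary measure. The false confirmation affects only samples that read low while their true value lies between the original limit and the raised floor. How many there will be, and what that does to the within-person differences, cannot be computed because the share of samples below range is not given. The finding is an error in a laboratory rule; it does not show bias in the planned analysis.

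**What to change.** Replace the one sentence in section 3.7 with two rules. (1) Samples above the upper limit are retested at a higher dilution. (2) Samples below the lower limit are retested at the same dilution or, where the assay protocol and the remaining volume allow, at a lower one; those still below range, or with too little blood left, are reported as below the limit and flagged as left-censored.

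The cost is a sentence or two and a matching line in the laboratory's instructions. It should be settled before the samples are assayed, because blood spent on an uninformative retest cannot be recovered.

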### Ultra-high field imaging

3.8

All MRI acquisitions will be performed on the Siemens MAGNETOM Terra 7T whole body scanner (Siemens Healthcare GmbH, Erlangen, Germany) utilizing ultra-high-field technology at the Center for Image Acquisition (CIA) at the University of Southern California. Below is a summary of each sequence type used in this project. See also Table 1 for a summary of the scan parameters.

**Table 1 tbl1:** Summary of scan acquisitions and parameters.

Scan Acquistion	Voxel Size (mm^3^)	# of Averages (NEX)	# of Slices (orientation)	FOV (cm)	TR/TE/TI (ms)	Flip Angle (°)	Phase Encoding Direction
**3D T1-weighted MRI**	1.1 × 1.1 × 1.0	1	192 (sagittal)	25.6	4300/1.84/840(inv1)/2370(inv2)	5.0(inv1)/6.0(inv2)	A/P
**rACC sLaser** **SVS MRS**	15 × 15 × 15	64	1 (axial)	NA	4000/29/NA	90	A/P
**dACC sLaser SVS MRS**	15 × 15 × 15	64	1 (axial)	NA	4000/29/NA	90	A/P
**L & R Hippocampus sLaser SVS MRS**	15 × 15 × 15	128	1 (axial)	NA	4000/29/NA	90	A/P

### T1-weighted anatomical MRI

3.9

A high-resolution 3D T1-weighted anatomical image will be acquired at both visits using a magnetization-prepared 2 rapid gradient echo (MP2RAGE) sequence (5 min 20 sec), with parameters tuned to optimize tissue contrast between gray and white matter at 7T. We will utilize the high-resolution images from this acquisition to prescribe more structurally accurate voxels in the MRS acquisition, implement structural processing pipelines, and to facilitate brain atlas registration of other image acquisitions in the processing pipeline.

### Magnetic resonance spectroscopy (MRS)

3.10

To characterize neurometabolic data, we will implement single-voxel (SV) magnetic resonance spectroscopy (MRS) imaging before and after the TSST. We will utilize the sLASER sequence for metabolite detection *in vivo*. A custom-made developed excitation pulse (EB 2000E, 4 ms) will be used for X slice selection and four refocusing pulses will be used for Y and Z slice localization (Kaiser et al., 2022) and VAPOR water suppression will be used. Optimization of transmit gain and higher order shimming will be performed prior to MRS acquisitions for each voxel of interest, including the rostral anterior cingulate cortex, dorsal anterior cingulate cortex, and the left and right hippocampus.

All metabolite concentrations will be estimated using fitting in LCModel (Provencher, 2009) and expressed as ratios relative to total creatine (i.e., creatine and phosphocreatine) as these levels are relatively high and stable across different tissue types in the brain and, thus, often used as an internal reference standard. Only voxels that have relative Cramer-Rao lower bounds (CRLBs) < 25% for the metabolite of interest will be considered in further analysis. Finally, the effects of fluid within each voxel will be corrected by dividing the metabolite concentrations by the fraction of non-fluid components (i.e., WM and GM). Given the dynamic cycling between glutamine and glutamate (extracellular glutamate is converted into glutamine in astrocytes before being released and taken up by neurons where it is synthesized into either glutamate or GABA), we will also consider the total sum of glutamate and glutamine (Glx), and the ratio of glutamine to glutamate, as complementary indices of glutamate metabolism (Brennan et al., 2017; Cooper et al., 2021).

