For all of the statistical analyses testing these hypotheses, potential demographic (e.g., age, gender), clinical (e.g., age of depression onset, number of comorbidities, presence of childhood trauma), or biological (e.g., percentage of gray matter in MRS voxel) covariates will be included if they are correlated with our outcome variables*.* Statistical significance will be set at α = 0.05. We will apply false discovery rate (FDR) correction as appropriate. In all simulation analyses for estimating sample size based on 1-β = 0.8, effect sizes (*r* or η2 or mean ± SD) were based on preliminary data or cited literature. For the hypotheses in Aims 2 and 3 that require logistic ridge regression analysis, we plan to sample 90% data as the training set and 10% as the testing set across 10 iterations; power was therefore calculated based on 90% of the sample after accounting for attrition (*N* = 108). We will put in rigorous effort to minimize missing data, including scheduling sessions around families’ availability, repeating scans when data were not useable due to movement or scan/user error, and providing bonus incentives for completing all follow-up assessments. For all longitudinal analyses, we will use flexible modeling approaches that allow individuals who provide at least one assessment to be included in our estimation of the effects of interests.

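### Dividing creatine-ratio metabolites by the voxel tissue fraction puts a spurious fluid term into Glu/tCr and Glx/tCr

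*Protocol article*

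**What the plan says.** Section 3.10 (Magnetic resonance spectroscopy) lists the processing in this order.

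1. All metabolite concentrations are fitted in LCModel and "expressed as ratios relative to total creatine (i.e., creatine and phosphocreatine"). The reason given is that creatine levels are "relatively high and stable across different tissue types in the brain and, thus, often used as an internal reference standard".
2. Voxels are kept only if the Cramer-Rao bound for the metabolite of interest is below 25%.
3. The next sentence, introduced as the last step, says that fluid effects "will be corrected by dividing the metabolite concentrations by the fraction of non-fluid components", which it identifies as white and gray matter.
4. The plan will also consider "the total sum of glutamate and glutamine (Glx), and the ratio of glutamine to glutamate, as complementary indices of glutamate metabolism".

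No water-referenced or otherwise unreferenced concentration is defined anywhere in the article.

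Two other places bear on the point. Section 3.6 (TSST) states that "our primary measures of inflammation and glutamate are *within-person differences* before and after the TSST". Section 2 (Study aims & hypotheses) says that "biological (e.g., percentage of gray matter in MRS voxel) covariates will be included if they are correlated with our outcome variables". Fluid fraction is not named as a covariate.

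**The concern.** Both steps deal with the same problem. Part of the voxel is fluid, which is taken to contribute no metabolite signal. A ratio to a reference from the same voxel removes that dilution, and so does division by the tissue fraction. Applied one after the other, the second step does not refine the first. It brings back, in inverted form, a dependence on fluid that the ratio had removed.

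Glutamate is the central imaging measure. It is an outcome in Aim 1, is compared between response groups and serves as the mediator in Aim 2, and is among the neural indicators in Aim 3. A measure that rises with voxel fluid for purely arithmetic reasons can appear related to anything else that varies with voxel fluid. The named covariate, gray matter percentage, is a different quantity, enters only conditionally, and would not reliably remove a multiplicative 1/f term.

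**Working it through.** **Inputs.** From section 3.10: the creatine reference and the later division by f = WM + GM fraction. From section 3.6: within-person differences as the primary form. The article gives no value of f and no figure that depends on this step, so there is nothing of the plan's own to reproduce. All f values below are assumptions.

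**Algebra.** Let G and C be the glutamate and total creatine concentrations in tissue. On the premise behind the plan's own division, fluid contributes neither.

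- Observed signals: Glu = G·f and tCr = C·f.
- Creatine ratio: (G·f)/(C·f) = G/C, which is free of f.
- After the further division: (G/C)/f.
- If Glu and tCr are each divided by f before the ratio is formed: (G·f/f)/(C·f/f) = G/C, so the division does nothing.

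Glx/tCr behaves in the same way. For glutamine over glutamate with both parts divided by f, the factor cancels.

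**Effect on levels**, 1/f − 1:

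| f (assumed) | Inflation |
|---|---|
| 0.95 | 5.3% |
| 0.90 | 11.1% |
| 0.80 | 25.0% |

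In a simulation with no true link between Glu/tCr and fluid, the divided value correlated with fluid fraction as follows. The undivided ratio correlated at about 0.00 throughout.

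| Fluid fraction, mean (SD), assumed | Between-person CV 12% | Between-person CV 8% |
|---|---|---|
| 10% (3%) | 0.27 | 0.39 |
| 15% (5%) | 0.44 | 0.59 |
| 20% (7%) | 0.59 | 0.74 |

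**Effect on pre/post-TSST differences with the same f at both scans.** An absolute change D becomes D/f. A true change of 0.065 (5% of an illustrative ratio of 1.3) becomes 0.065/0.90 = 0.072, 0.065/0.80 = 0.081 or 0.065/0.70 = 0.093. Percent change is untouched, because f divides both values.

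**Effect if f is re-estimated and differs between scans.** With no true change, the false change is f_pre/f_post − 1:

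- f from 0.90 to 0.88: 0.90/0.88 − 1 = +2.3%.
- f from 0.85 to 0.82: 0.85/0.82 − 1 = +3.7%.
- f from 0.85 to 0.80: 0.85/0.80 − 1 = +6.3% (6.25% unrounded).

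**The case against.** **The wording allows a harmless reading.** The sentence speaks of dividing metabolite concentrations, not ratios, and creatine is itself a fitted concentration. If everything including creatine is divided by f before ratios are formed, f cancels. This is possible, but it runs against the stated order, in which the ratio comes first and the division is introduced as the last step. It also makes the step pointless. The sentence needs correcting on either reading.

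**The article condenses a fuller protocol.** That would excuse an omission. Here a specific procedure is stated, and it is the stated procedure that fails.

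**Scope.** A reader might infer that every glutamate index is affected. The article does not say that Gln/Glu is itself divided by f, and the factor cancels if both its parts are. This objection stands.

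**Loss of information.** A reader might add the variance of 1/f to that of glutamate. Take 108/0.9 = 120 participants, an assumed between-person CV of 8%, and a CV of 1/f between 3.5% and 8.8%. Variance then rises by 1 + (3.5/8)² = 1.19 to 1 + (8.8/8)² = 2.21, and 120 participants would count as 120/1.19 = 101 down to 120/2.21 = 54. That calculation is for single levels, whereas section 3.6 makes within-person differences primary. With f constant within a session and D independent of f, the relative efficiency for the mean of D/f is 1/[1 + CV²(1 + d²)], where d is the standardised change. At CV = 0.088 and an assumed d = 0.5 this is 1/(1 + 0.00774 × 1.25) = 0.990, or about 119 of 120. The loss is about 1%, so the larger figures are not supported.

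**False pre/post change.** A reader might infer that any voxel shift creates one. The 1/f term does this only if f is estimated separately for the two scans. The article does not say so, and section 3.9 describes one anatomical image at each visit, which is compatible with a single f per session. The mechanism is conditional. It is more plausible between T1 and T2, which are 12 weeks apart with a separate anatomical image each time, for example when exploring whether SSRIs affect glutamate (Discussion).

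**Conclusion.** Wrong as written. Taken in the order given, the two steps leave a spurious 1/f factor in Glu/tCr and Glx/tCr. This follows by algebra from the plan's own premise that metabolites lie in tissue and not in fluid. The factor makes levels depend on voxel fluid and scales absolute TSST changes up in participants with more fluid. It adds a false change wherever f is re-estimated and differs between scans.

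The size cannot be fixed from the article. The 5% to 25% inflation of levels and the false changes of a few percent illustrate assumed f values. The documents do not support a material loss of power for the primary within-person differences when f is constant within a session. The problem there is a fluid-dependent scale on the measure. No stated sample size or significance level depends on this step.

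**What to change.** Amend the processing text in section 3.10 as follows.

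- Delete the division by the tissue fraction for all creatine-ratio measures, and state that the undivided creatine ratio is primary.
- Keep tissue composition as a covariate.
- Apply the division only to concentrations not referenced to creatine (for example water-referenced values), if these are available, and report them as a sensitivity analysis.

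The cost is a sentence or two. No new data are needed, and the fitted spectra can be reprocessed. Settling it before analysis also avoids choosing between two glutamate definitions once results are known.
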